#### Intervention group

Participants will be provided with the MBI, plus treatment as usual, divided into 24 patients diagnosed with a first episode of schizophrenia and 24 patients in a high-risk mental state (groups do not include both profiles). This means that both groups will be submitted to eight sessions of mindfulness workshops adapted for patients with psychosis [17]. The proposed duration for each session is 1 hour and a half, once a week. The intervention will take place in the facilities of each participating clinical center and led by a mindfulness coach with specific training in the target audience. The main project researcher will supervise and train each coach in the application of mindfulness in psychosis. The workshop includes take-home exercises. Additionally, every participant will get a pen drive or CD with guided mindfulness practice audios and a booklet with the contents of each session. Groups will be composed of up to eight members and two workshops have been planned by every participating institution.

#### Control group

Participants will receive standard care for this illness (treatment as usual), in other words, pharmacology and psychosocial intervention under clinical guidelines (e.g., social skills workshop).

The assessment, application of neuropsychological tests (Measurement and Treatment Research to Improve Cognition in Schizophrenia (MATRICS) Battery), and self-reporting questionnaires will take place (1) before the workshop; (2) after the workshop; and (3) at follow-up 3 months after completing the workshop. Additionally, 4 weeks after completing the workshop, participants will be submitted to semi-structured interviews. The number of interviews will be defined based on the saturation of the concepts found in the qualitative methodology. Each interview will last approximately 20 minutes and will be performed by a member of the research team.

### Measuring instruments

#### Primary outcome

The primary outcome will be the cognitive function through MATRICS. This battery assesses seven functioning areas, namely speed of processing, attention/vigilance, working memory, verbal learning, visual learning, reasoning and problem solving, and social cognition. The assessment takes place through seven tests.

#### Secondary outcomes

##### Psychological well-being/positive dimension (increase)

The following instruments will be used to assess the psychological well-being in its positive dimension:Psychological well-being scale [52, 53], which includes 39 items grouped in six subscales: self-acceptance, positive relations with others, autonomy, environmental mastery, purpose in life, and personal growth. Respondents answer in the Likert scale format with a range from 1 to 6 (1 = strong disagreement and 6 = strong agreement). This scale has been broadly studied to assess psychological well-being. The version validated in Chile and published by Véliz-Burgos will be used [54].Self-esteem scale by Rosenberg. This is a 10-item scale broadly used in research. It is a uni-dimensional instrument answered with a Likert scale of four options, ranging from “strongly agree” to “strongly disagree”. The Chilean version showed adequate psychometric properties [55].Five Facet Mindfulness Questionnaire [56], which is a self-reporting questionnaire that describes mindfulness operationally as a multidimensional construction, built on the following five facets: observing, describing, acting with awareness, non-judging of experiences, and non-reactivity to experience. The questionnaire uses a Likert scale ranging from 1 (never or very rarely true) to 5 (very often or always true). It presents adequate psychometric properties in the Chilean population [57].

##### Psychological well-being/symptomatology dimension (reduction)

The following instruments will be used to measure the symptomatic dimensions of psychological well-being:Positive and Negative Affect Schedule (PANAS) [58], which is a 20-item scale including by 10 items that assess positive affect and 10 items that assess negative affect. Items are formed by words that describe different feelings and emotions. The Chilean version published by Dufey and Fernández will be used [59].Penn State Worry Questionnaire (PSWQ-11) [60], which is a measure of worry phenomena designed to assess the general trends when experiencing worry. It is composed by 16 items to which participants respond in a 5-score Likert scale, ranging from 1 “not at all typical of me” to 5 “very typical of me”. The Spanish version of Sandin, Chorot, Valiente and Lostao will be used, which has shown to have adequate psychometric properties [61].Depression, Anxiety and Stress Scale (DASS-21) [62]. This is a self-applied scale that assesses general symptoms in three dimensions. Seven items are related to depression symptoms, seven to anxiety symptoms, and seven to stress. The scale has been validated in Chile with good psychometric properties [63].

### Data analysis

A mixed qualitative and quantitative analysis method will be used. Qualitative information will be collected by means of semi-structured interviews and assessed with the Grounded Theory. This data analysis approach is widely used in social sciences and was previously applied for the analysis of the subjective experience of patients with psychosis [26]. This methodology will analyze the patients’ subjective experience regarding the feasibility and contribution of this type of intervention in a local context. At the quantitative level, the hypothesis will be contrasted though a mixed designed ANOVA in order to consider both the impacts of the intervention (inter subjects) and time (intra-subject; pre, post, and follow-up measurements) in every variable assessed. The analysis will help prove the hypotheses regarding the efficiency of this intervention in both patient groups. If statistically significant differences are found between the trial and control groups at the beginning of the intervention, corrections will be conducted using an ANCOVA.

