The purpose of this study is to determine how efficient MBIs can be in increasing cognitive functions and psychological well-being in patients with a first episode of schizophrenia and patients in a high-risk mental state, and thus define the scope of mindfulness to increase these areas of functioning. The specific goals are to (1) determine how efficient a mindfulness intervention can be in increasing attention, working memory, and social cognition rates, compared with the control group; (2) establish which spheres of psychological well-being increase (positive dimension) and which decrease (symptomatic dimension) with mindfulness training, compared to the control group; (3) determine whether the expected outcomes (increased cognitive functions and psychological well-being) are still present 3 months after the intervention has finalized, and additionally establish whether impacts are greater in participants who continue practicing mindfulness compared to those who fail to continue the practice; and (4) describe, on the one side, the subjective experience of patients regarding the feasibility of implementing such an intervention in a local context and, on the other, the benefits of mindfulness for patients compared to other psychosocial interventions in the context of mental health public policies in Chile.

The hypotheses are as follows. (1) MBIs will increase executive functions. Specifically, a statistically significant increase is expected in attention, working memory, and social cognition rates compared to the control group. (2) Subjective psychological well-being rates will increase significantly in the mindfulness group compared to the control group. (3) The outcomes in the areas described will persist 3 months after; however, impacts will be greater on people who continue practicing mindfulness compared to those who do not.

The questions that guide the qualitative goals are as follows. (1) What were the benefits and shortcomings found during the workshop? (2) Do patients continue with this practice and mainstream the outcomes into other areas of their lives? (3) What differences and similarities are perceived by patients between mindfulness and traditional psychosocial interventions?

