### Participants

Patients will be recruited from six clinical centers from three different cities in Chile; four in Santiago, one in Valdivia, and one in Osorno. Ninety six people are expected to take part in the study, of which 48 will be patients diagnosed with a first episode of schizophrenia (divided into 24 trial and 24 controls) based on the following criteria: patients with a psychotic episode without a prior diagnostic of schizophrenia, patients diagnosed with schizophrenia for the first time, and/or patients who persist with the schizophrenia diagnosis after the first episode. Additionally considered is the participation of 48 patients under a high-risk mental state (divided into 24 trial and 24 controls) who meet the criteria of an Attenuated Psychosis Symptom Syndrome, including delusional beliefs, attenuated hallucinations, and disorganized speech with intact reality testing but of sufficient severity and/or frequency that it is not discounted or ignored [5]. Sample size was estimated considering a previous RCT for people with schizophrenia on both the MBI [20] and a cognitive remediation program [50]. The sample size was calculated by using the statistical program G*Power [51]. The sample required to detect statistically significant differences in the cognitive functioning for a two-tailed test of the proportions with an effect size of 0.80, an alpha of 0.05, and a power of 0.90 is 2 × 39. With an estimated 15–20% drop-out over 3 months, we decided to include 96 persons in the trial, 48 allocated in each intervention arm. The inclusion criteria are (1) patients diagnosed with a first episode of schizophrenia or in high-risk of psychosis, as applicable; (2) aged between 15 and 35 years; and (3) clinical stability defined by medical and psychometric criteria (e.g., PAANS). Exclusion criteria are (1) risk of suicide; (2) severe intellectual disability (mental retardation); (3) medical illness inconsistent with the intervention; and (4) substance abuse or dependence in the past 6 months. Figures 1 and 2 summarize the process of randomization, group allocation, and assessment. The SPIRIT checklist is available in Additional file 1.

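### The three-visit mixed-design ANOVA leaves the deciding contrast unnamed, adjusts for baseline only conditionally and, in its classical form, discards participants who miss one visit

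*Protocol article*

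**What the plan says.** All of this is in the protocol article; no separate analysis plan is shown.

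- **Model.** Data analysis states that "the hypothesis will be contrasted though a mixed designed ANOVA in order to consider both the impacts of the intervention (inter subjects) and time". Time has three levels, one of them the pre-workshop measurement, and the model applies to every outcome. No arm-by-time interaction and no contrast at a given visit is mentioned.
- **Baseline.** The same section continues: "If statistically significant differences are found between the trial and control groups at the beginning of the intervention, corrections will be conducted using an ANCOVA". Otherwise there is no adjustment.
- **Hypotheses** (end of the Background). For hypothesis 1, "a statistically significant increase is expected in attention, working memory, and social cognition rates compared to the control group". Hypothesis 2 makes the same kind of claim for well-being. Hypothesis 3 begins: "The outcomes in the areas described will persist 3 months after".
- **Sample size** (Participants). The calculation is for a "two-tailed test of the proportions with an effect size of 0.80", alpha 0.05 and power 0.90, giving 39 per arm. "With an estimated 15–20% drop-out over 3 months", this is raised to 48 per arm, 96 in all.

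**The concern.** Hypotheses 1 and 2 claim a larger gain than control by the end of the workshop. Hypothesis 3 claims that the gain is still there 3 months later. These are arm differences at two particular visits, relative to baseline. The planned model contains a visit at which randomisation makes the expected arm difference zero, and the text attaches the intervention to the between-subject factor without naming the comparison that decides.

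Three things are at stake:

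- **Choice of term.** The main effect and the interaction can give different answers. The text does not fix which one counts, so the choice could be made after the results are seen.
- **Baseline adjustment.** Making it depend on a significance test means giving up its precision in most trials.
- **Partial data.** A classical mixed-design ANOVA uses only participants seen at every visit. Someone tested before and after the workshop but absent at 3 months is lost from the post-workshop comparison too.

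**Working it through.** **Inputs.** From the protocol article: effect 0.80, two-sided alpha 0.05, power 0.90, 39 per arm required, 48 per arm randomised, 15–20% drop-out, three visits. Assumed, because the article gives none: SD 1 at each visit, the same correlation r between any two visits (0.5 to 0.8, with 0.3 as a lower check), and a true effect of 0 before the workshop and 0.80 SD at both later visits.

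**1. The plan's own figure.** Taking 0.80 as a standardised mean difference, a two-sample t-test needs 34 per arm for power 0.90, and 39 per arm gives 0.937. The stated 39 is therefore not reproduced from the stated inputs. This does not decide the present point.

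**2. Completers.** 48 × 0.85 = 40.8 and 48 × 0.80 = 38.4. A completers-only analysis keeps about 38 to 41 per arm, close to the planned 39. The power figures below use 38.

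**3. Between-subject main effect.** It estimates (0 + 0.80 + 0.80)/3 = 0.53 SD. A participant's three-visit mean has variance (1 + 2r)/3, so the standardised effect is 0.533/√((1 + 2r)/3).

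**4. Arm-by-time interaction of the same ANOVA.** The noncentrality is (n/2) × Σ(m − m̄)²/(1 − r), on 2 and 148 df. For arm differences of 0, 0.80, 0.80 the sum is 0.284 + 0.071 + 0.071 = 0.427, so the noncentrality is 19 × 0.427/(1 − r).

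**5. Baseline-adjusted comparison at one visit.** The standardised effect is 0.80/√(1 − r²).

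| r | Main effect: size, power | Interaction: noncentrality, power | Adjusted, one visit: size, power |
|---|---|---|---|
| 0.3 | 0.730, 0.88 | 11.6, 0.86 | 0.84, 0.95 |
| 0.5 | 0.653, 0.80 | 16.2, 0.955 | 0.92, 0.98 |
| 0.7 | 0.596, 0.73 | 27.0, 0.998 | 1.12, 0.998 |
| 0.8 | 0.573, 0.69 | 40.5, >0.99 | 1.33, >0.999 |

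**6. What the interaction cannot tell.** Suppose the effect is 0.80 after the workshop and gone at 3 months: differences 0, 0.80, 0. The sum is 0.071 + 0.284 + 0.071 = 0.427, the same as in step 4. The omnibus test has the same power for an effect that persists as for one that vanishes, so a significant result does not speak to hypothesis 3.

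**7. Conditional baseline adjustment.** Under randomisation, a baseline test at the 5% level (an assumed level) triggers adjustment in about 1 trial in 20. Unconditional adjustment at a single visit multiplies the residual variance by 1 − r², which is 0.75, 0.51 and 0.36 at r = 0.5, 0.7 and 0.8.

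**8. Drop-out bias, illustration only.** Assume r = 0.7, a true effect of 0.50 SD and 20% lost at 3 months in each arm. In the intervention arm the odds of loss rise 2.7-fold per SD lower post-workshop score; in the control arm loss is random. The completers-only post-workshop difference is then 0.67, while all observed post-workshop scores give 0.50. Part of the excess also appears at baseline: 0.7 × 0.17 = 0.12. A change-from-baseline comparison in completers would therefore show 0.67 − 0.12 = 0.55, a smaller bias but not zero. With a true effect of 0, the raw completers-only difference is 0.17. If loss is unrelated to outcome there is no bias: in a parallel check with r = 0.6, the completers' 3-month difference was 0.79 for a true 0.80.

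**The case against.** The labels in "the impacts of the intervention (inter subjects) and time (intra-subject; pre, post, and follow-up measurements) in every variable assessed" are the ordinary names for the two factors of a mixed design. Such an ANOVA also yields the arm-by-time term. The hypotheses are worded as increases relative to control, and the ANCOVA sentence treats a baseline difference as something to correct, so the authors probably do not regard the baseline visit as evidence of effect. This stands. A reader might infer that the plan commits to the main effect and that the trial is therefore underpowered, but the text does not establish this. Over r = 0.5 to 0.8 the interaction exceeds the stated 0.90. At r = 0.3 both terms fall slightly short.

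No sentence says that participants with a missing visit are excluded. Exclusion is a property of the classical method, and missing-data rules may sit in a plan that is not shown. The enlargement to 96 already pays for the lost numbers. The standard error is 12% larger with completers than with everyone (√(1/0.8) = 1.12), but only against a full 48 per arm, which the plan never assumed. The bias needs drop-out that depends on outcome differently by arm. In the illustration it exaggerates the effect, so it does not act in the same direction as the dilution. All of this stands too.

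Follow-up contrasts are often left to an analysis plan. Here, however, the article does state the model and the baseline rule, and the criticism is of those stated choices. Neither the main effect nor the omnibus interaction answers hypotheses 1 and 3 separately, and the conditional ANCOVA is explicit.

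**Conclusion.** The point holds as a worthwhile change to the analysis, not as a proven loss of power or a demonstrated bias. What the document supports is a three-visit ANOVA with no named deciding contrast, and baseline adjustment that depends on a significance test.

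The rest is conditional:

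- **Dilution.** 0.80 to 0.53 SD, with power of 0.69 to 0.80, only if the between-subject main effect is the test. These figures assume 38 per arm, equal visit correlations of 0.8 to 0.5 and the same effect at both later visits.
- **Missing visits.** Loss of partly observed participants only if the ANOVA is run in its classical form. The numbers lost are already budgeted for.
- **Bias.** 0.67 for a true 0.50 only under the assumed drop-out pattern, and for the raw difference. It is 0.55 for change from baseline.

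The inability of the omnibus interaction to distinguish a lasting effect from a vanishing one does not depend on drop-out.

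**What to change.** Replace the mixed-design ANOVA and the conditional ANCOVA with a likelihood-based mixed model for repeated measures on the post-workshop and 3-month scores:

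- fixed effects for arm, visit, arm × visit and baseline score × visit, with unstructured covariance;
- baseline adjustment always, with no preliminary test;
- every randomised participant with at least one post-baseline score, in the arm assigned;
- hypotheses 1 and 2 tested by the arm contrast at the post-workshop visit, and the persistence part of hypothesis 3 by the arm contrast at 3 months.

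Naming two baseline-adjusted visit contrasts within the existing approach would settle which test decides, but would not keep partial data.

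**Cost.** A change of wording and slightly more programming; no new data, visits or participants.

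**Limits.** Validity still rests on scores being missing at random given the observed ones. Participants who leave before the post-workshop visit and are not seen later contribute no outcome. The part of hypothesis 3 that compares those who keep practising with those who stop is a separate question that this model does not answer.

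### The primary outcome is not tied to one testable variable or set: seven areas in the outcome section, three in hypothesis 1, one test in the sample size, and no rule for primary success

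*Protocol article*

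**What the plan says.** Four places in the protocol article bear on this.

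- **Measuring instruments, Primary outcome:** "The primary outcome will be the cognitive function through MATRICS", followed by "This battery assesses seven functioning areas". No composite score and no lead area is named. The Abstract gives the same primary outcome.
- **End of the Background, goals and hypotheses:** under hypothesis 1, "a statistically significant increase is expected in attention, working memory, and social cognition rates compared to the control group". Specific goal 1 names the same three areas, and the closing Discussion frames the expected conclusion on them.
- **Participants, sample size:** "The sample required to detect statistically significant differences in the cognitive functioning" is given as 39 per arm, for a two-sided test with effect size 0.80, alpha 0.05 and power 0.90. This is the only significance level in the document. It is not split, and it belongs to a single comparison.
- **Data analysis:** the hypothesis is examined by a mixed-design ANOVA with arm as the between-subject factor and time as the within-subject factor ("intra-subject; pre, post, and follow-up measurements) in every variable assessed"). No per-test level and no criterion for primary success is stated.

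**The concern.** These statements do not describe the same primary test. The outcome section points to a battery of seven areas, the hypothesis to three, and the sample size to one comparison. The analysis gives every measured variable its own model.

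A reader of the final report could not tell from this text whether the primary result was positive if, for example, working memory were significant and attention and social cognition were not. Nor is it clear whether a significant result in one of the four areas outside hypothesis 1 would bear on the primary outcome. The choice could then be made after the results are known. The stated alpha of 0.05 and power of 0.90 cannot both be relied on until the primary set and the success rule are fixed.

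**Working it through.** **Inputs from the document.** Seven areas in the battery (Primary outcome); three in hypothesis 1 (end of Background); effect size 0.80, two-sided alpha 0.05, power 0.90, 39 per arm, drop-out 15–20%, 48 randomised per arm (Participants).

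**Assumptions.** Each domain is tested at 0.05, carried over from the sample-size paragraph. The effect size is read as a standardised mean difference d. The correlation between domain test statistics is not given, so a range from 0 to 0.9 is shown.

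**1. The plan's own figure.** n per arm = 2(1.960 + 1.282)² / 0.80² = 32.8, so 33. The exact two-sample t-test gives 33.8, so 34. The arcsine test of proportions with h = 0.80 also gives 33. The stated 39 is not reproduced by these usual formulas, but it errs on the large side and does not affect this point. Drop-out is consistent: 39/0.85 = 45.9 and 39/0.80 = 48.75, against 48 planned. With 39 per arm, d = 0.80 and alpha 0.05, t-test power is 93.7%.

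**2. If any one significant domain counts as success.** For k independent tests, P(at least one false positive) = 1 − 0.95^k:
- k = 3: 1 − 0.857 = 14.3%
- k = 7: 1 − 0.698 = 30.2%

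For correlated domains (equicorrelated normal test statistics, 1,000,000 simulated draws, all nulls true):

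| Assumed correlation | 3 domains | 7 domains |
|---|---|---|
| 0 | 14.3% | 30.2% |
| 0.3 | 13.6% | 27.1% |
| 0.5 | 12.5% | 23.0% |
| 0.7 | 10.9% | 17.8% |
| 0.9 | 8.3% | 11.4% |

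The error exceeds 5% throughout this range.

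**3. If all three domains must succeed.** There is no inflation. With all nulls true, the simulated error is at most 2.3% (at correlation 0.9), and in general it cannot exceed 5%. Joint power for three independent domains, each with d = 0.80, is 0.937³ = 0.82. Correlation raises this, up to 93.7% in the limit of perfect correlation. The stated 90% is therefore not assured.

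**4. If the three domains are tested with Holm.** The strictest step is 0.05/3 = 0.0167. Power there with 39 per arm and d = 0.80 is 85.8%. Reaching 90% at that step needs 43.7, so 44 evaluable per arm.

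**The case against.** The strongest reply is that much of the alarm comes from a rule the protocol never states. Data analysis gives no per-test level, and hypothesis 1 is worded jointly, which fits a requirement that all three areas improve. On that reading alpha is not inflated. The sentence listing seven areas may only describe the battery, and an overall cognitive score is neither named nor excluded. An adjustment for multiple tests may also sit in an analysis plan that is not shown.

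Most of this stands, and it limits the percentages to conditional statements. It does not remove the point. Which variable is primary is something this article does state, and its statements disagree. An adjustment cannot be defined until the family is known to be one, three or seven tests. The joint reading also leaves the stated 90% power unassured.

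Stronger inferences are tempting but unsupported:
- **Extra chances by visit.** A reader might think that success at either the post-workshop or the 3-month assessment adds to the error. The plan describes one ANOVA per variable covering all visits, with no separate tests by visit. Persistence at 3 months is a hypothesis of its own.
- **Doubling by diagnosis.** A reader might count three domains in each of two diagnostic groups and obtain 1 − 0.95⁶ = 26.5%. The text says "The analysis will help prove the hypotheses regarding the efficiency of this intervention in both patient groups", but it describes no separate test in each group, and the figure again assumes that any one result suffices.

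**Conclusion.** The point holds as an inconsistency in how the primary outcome is defined, together with the lack of a success rule. It is not a demonstration that the trial's false-positive rate is 14% or 30%. Those figures apply only if one significant domain at 0.05 counts as primary success: about 8–14% for three domains and 11–30% for seven, over assumed correlations from 0.9 to 0. Under an all-three rule the error stays within 5%, and the weakness moves to power: about 82% with independent domains and d = 0.80 in each, more if they are correlated. The sample-size paragraph's alpha and power match a single test, and the protocol does not say which test that is.

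**What to change.** Before post-workshop outcome data exist, state in the protocol and analysis plan that the primary set is the three domains of hypothesis 1, tested by Holm at an overall two-sided 0.05, with a claim only for the domains that pass. Declare the other four areas of the battery secondary. A single pre-specified overall cognitive score tested at 0.05 would be an acceptable alternative and would match the sample-size paragraph more closely. Either way, use the same definition in the Abstract, outcome section, hypotheses, sample size and Data analysis.

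The cost is wording plus some power. With Holm, power for d = 0.80 at the strictest step with 39 per arm is about 86%, below the stated 90%, so that figure should be restated. Holding 90% at that step would take 44 evaluable per arm, or 44/0.85 = 52 to 44/0.80 = 55 randomised per arm, against 48 planned. The fix does not require that increase. It also does not depend on any change to the time point, covariates or analysis population. The Trial status section places the trial in recruitment with workshops still to start, so as the article stands the choice could still be made in time.

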## Discussion

Schizophrenia is a chronic and severe mental health disorder. In Chile, it is a public health priority subject to integral treatment indications (pharmacological and psychosocial). There is abundant empirical evidence suggesting that MBIs are feasible and beneficial interventions for patients with schizophrenia. MBIs promote a more flexible relationship with the psychotic symptoms, with impacts on the patients self-awareness and own resources and not only on the shortcomings and limitations of having a chronic mental illness [7, 16, 29]. However, one of the elusive areas in targeting these psychotherapeutic treatments are cognitive impairments [7], while an adequate cognitive functioning has clear impacts on the psychological well-being of patients [64].

All the scientific evidence points to the need to study the relationship suggested in this project, i.e., to determine the impact of mindfulness on cognitive functions and the psychological well-being in people with schizophrenia. However, it is also worthwhile to include people with a high-risk mental state since this could provide insights in several areas, including (1) proving the efficacy of the MBI intervention for this group; (2) comparing the outcomes with those of patients with a first episode of schizophrenia (i.e., determine the scope of mindfulness according to the pathology level); and (3) allow subjective assessment of the mindfulness benefits according to patient experience when facing a reduction in psychological discomfort.

Thus, this study aims, on the one hand, to discuss different aspects that have not yet been addressed in the literature concerning MBIs applied in psychosis and, on the other, to confirm previous findings in other social and cultural contexts so as to improve the ecological soundness of this intervention [28]. In addition, the insights provided by self-reporting studies need to be improved through more accurate measurements such as neuropsychological tests.

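### The 0.90 power covers only the two diagnoses pooled, yet the analysis section claims a conclusion in both patient groups, from a model described with intervention and time only

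*Protocol article*

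**What the plan says.** **Sample size (Participants).** There is one calculation, for a two-sided test on cognitive functioning that the text calls a test of proportions. Its inputs and result are given as "with an effect size of 0.80, an alpha of 0.05, and a power of 0.90 is 2 × 39". The number is then raised to allow for 15–20% attrition, and the text concludes: "we decided to include 96 persons in the trial, 48 allocated in each intervention arm". The 48 per arm mix both diagnoses. The same section splits them: 96 people, "of which 48 will be patients diagnosed with a first episode of schizophrenia (divided into 24 trial and 24 controls"), and the same split of 48 for the high-risk group. No power is given for either diagnosis alone.

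**Model and conclusion (Data analysis).** The quantitative analysis is a mixed-design ANOVA with intervention between subjects and time (pre, post, follow-up) within subjects. Diagnosis is not mentioned as a factor, and no separate analysis per diagnosis is described. The next sentence is "The analysis will help prove the hypotheses regarding the efficiency of this intervention in both patient groups".

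**Discussion.** Including high-risk patients is justified by insights it could bring. These include showing efficacy in that group and "comparing the outcomes with those of patients with a first episode of schizophrenia". The goals and hypotheses at the end of the Background set mindfulness against control; they contain no comparison between diagnoses.

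**The concern.** The article fixes the size of the trial for one question (does the intervention work over both diagnoses together?) and then states a conclusion about each diagnosis. The model as described has no term that speaks to a single diagnosis. If a separate ANOVA per diagnosis is meant instead, each runs on half the patients.

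What is at stake is how a mixed result would be read. Suppose the intervention works equally well in both groups at the planned effect. With 24 v 24 or fewer, there is a sizeable chance that one group reaches significance and the other does not. Readers who take the stated power of 0.90 to cover each group could then conclude that mindfulness helps one diagnosis and not the other, when the contrast is only sampling noise.

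**Working it through.** **Inputs from the article (Participants).** Effect size 0.80; two-sided alpha 0.05; power 0.90; 39 per arm required; drop-out 15–20%; 48 per arm enrolled; 24 v 24 in each diagnosis. *Assumption:* 0.80 is a standardised mean difference at one time point, analysed by a two-sample t-test. The article does not say which effect-size measure it used.

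**1. The plan's own figure.** A two-sample t-test with these inputs needs 34 per arm (33 by the normal approximation), so 39 does not follow directly. A continuity-corrected proportions test can give 38 or 39 for assumed control rates of 0.15 to 0.50, but no rates are stated. In any case 39 is on the safe side.

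Drop-out: 39/0.85 = 45.9 → 46 and 39/0.80 = 48.75 → 49. The 48 chosen corresponds to a drop-out of 1 − 39/48 = 18.75%.

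**2. Patients per diagnosis after drop-out.** 24 × 0.85 = 20.4 and 24 × 0.80 = 19.2, so about 19 to 20 per arm.

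**3. Power at 0.80.** Noncentral t, noncentrality 0.80 × √(n/2), df = 2n − 2.

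| Comparison | n per arm | Noncentrality | Power |
|---|---|---|---|
| Pooled, enrolled | 48 | 3.92 | 0.97 |
| Pooled, required | 39 | 3.53 | 0.94 |
| One diagnosis, no drop-out | 24 | 2.77 | 0.77 |
| One diagnosis, after drop-out | 20 | 2.53 | 0.69 |
| One diagnosis, after drop-out | 19 | 2.47 | 0.67 |

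The effect detectable with power 0.90 in one diagnosis is 0.96 SD at 24 per arm and 1.05 to 1.08 SD at 20 to 19. Reading 0.80 as the arcsine effect size for proportions, with the same assumed control rates, gives 0.78–0.79 at 24 per arm and 0.67–0.71 at 19–20. The picture does not change.

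**4. Outcome in both diagnoses, if the true effect is 0.80 in each.** The groups are independent.

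- Both significant: 0.774² = 0.60 at 24 per arm; 0.693² = 0.48 at 20; 0.670² = 0.45 at 19.
- Exactly one significant: 2 × 0.774 × 0.226 = 0.35 at 24; 2 × 0.693 × 0.307 = 0.43 at 20; 2 × 0.670 × 0.330 = 0.44 at 19.

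**5. Difference in effect between diagnoses.** SE = √(4/n per cell) in SD units; power ≈ Φ(difference/SE − 1.96).

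- n = 24: SE 0.408; 0.80/0.408 = 1.96; power 0.50.
- n = 20: SE 0.447; 0.80/0.447 = 1.79; power 0.43.
- n = 19: SE 0.459; 0.80/0.459 = 1.74; power 0.41.

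For a difference of 0.40, power is 0.16 at 24 per cell and 0.14 at 19 to 20.

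**The case against.** **The sentence is hedged and ambiguous.** It says the analysis will help prove the hypotheses, and naming both groups may only describe the study population. That is a fair reading, and it is why clarification is the right remedy. But if the sentence means the pooled population, it should not be worded as a result in both groups. If it means one ANOVA per diagnosis, the 24 v 24 shortfall applies in full.

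**Model terms belong in the analysis plan.** An article may leave covariates and subgroup terms to a fuller document, so the absence of diagnosis from the model would be no finding by itself. The point is that this article names the factors and the conclusion side by side, and they do not match.

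**The t-test is not the planned analysis.** This stands. If 0.80 is on the raw score, baseline adjustment acts like an effect of 0.80/√(1 − r²). At an assumed pre-post correlation of 0.5 that is 0.92, with power 0.79–0.88 at 19–24 per arm. At 0.7 it is 1.12, with power 0.92–0.97. A change-score analysis gives 0.67–0.77 and 0.87–0.94. The article states no correlation, uses none in its calculation, and reserves ANCOVA for groups that differ at baseline. Even so adjusted, the test of a between-diagnosis difference of 0.80 at 20 per cell would have power of only Φ(0.92/0.447 − 1.96) = 0.54 or Φ(1.12/0.447 − 1.96) = 0.71.

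**Two stronger readings are tempting and not supported.** A reader might infer that the trial commits itself to comparing the diagnoses. It does not: the comparison is a possible insight in the Discussion and is absent from the stated hypotheses. A reader might also infer that leaving diagnosis out inflates the error of the main test. A constant difference in score between diagnoses is present at every visit and cancels in the arm-by-time test; only the arm main effect, averaged over visits, would lose precision. Nor would pooling bias the arm effect, since 24 v 24 is planned within each diagnosis.

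**Conclusion.** The point holds as a mismatch between what is powered and modelled and what is to be concluded. The pooled comparison meets the stated 0.90 at an effect of 0.80. A conclusion in each diagnosis does not on the t-test basis: power is 0.77 at best and 0.67 to 0.69 after the stated drop-out, and significance in both groups is close to a coin toss after drop-out. The between-diagnosis comparison has power of about 0.41 to 0.43 after drop-out, even for a difference as large as the whole planned effect.

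The figures assume a single-time-point t-test and a true effect of 0.80. A high pre-post correlation with baseline adjustment could bring per-group power to 0.90. A smaller effect works the other way: at 0.5 SD it is 0.32 to 0.40. This is a worthwhile, inexpensive correction to what the trial may claim, and not a flaw in its main comparison.

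**What to change.** 1. Name the pooled arm-by-time effect as the confirmatory comparison.
2. Add diagnosis and the arm-by-diagnosis-by-time term, with its lower-order terms, to the model.
3. Report the effect in each diagnosis as an estimate with a confidence interval, labelled exploratory.
4. Compare the diagnoses only through the interaction term, never by setting one group's p-value against the other's.
5. State that the 0.90 applies to the pooled comparison, and give per-group power beside it: about 0.67 to 0.77 on the t-test basis, or a better-founded figure if a pre-post correlation can be justified.
6. Reword the sentence on both patient groups to match.

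**Cost.** Some wording and a few model terms; no more patients. The downside is a less favourable claim for each group. If confirmatory conclusions per diagnosis are really wanted, 0.90 power at 0.80 by t-test needs 34 per arm in each diagnosis: 4 × 34 = 136 analysed, or 4 × 40 = 160 to 4 × 43 = 172 enrolled at 15–20% drop-out, against the 96 planned.
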